### 2.7. Methods to Facilitate Sustainability

A community of practice (CoP) will be developed to support therapists in the implementation of evidence-based SENSe therapy. Initially, this community will be developed locally as part of the peer group upskilling of therapists at SENSe therapy centers. A website and online presence will be developed to enhance this CoP and provide ongoing education and peer support in the sustained implementation of evidence-based SENSe therapy. The website will connect therapists, provide support and information with case scenarios, and permit interactive feedback.

### 2.8. Data Analysis

Data management and data statement: Due to the personal nature of the data and original ethics approval, the data will not be made available broadly. De-identified data may be made available for related research and analyses by the research group and collaborators with additional ethics approval. Data will be entered using the REDCap electronic data capture tools [56], hosted at the Florey Institute of Neuroscience and Mental Health, by the site coordinator or trained delegate. REDCap features are in place to ensure valid data capture (e.g., data range checks), and data quality checking procedures are in place to ensure accuracy at initial entry and subsequently checked by a second independent researcher. Data will be de-identified for analyses. All data will be kept secure and confidential as per the approved ethics protocol.

Access to evidence-based sensory rehabilitation: The number of stroke survivors who receive SENSe therapy by therapists credentialled in SENSe therapy will be calculated. Successful completion of SENSe therapy for a survivor of stroke is determined as delivery of 7 or more therapy sessions. The number of attempted deliveries of SENSe therapy that did not meet the criterion for successful completion will also be counted.

Effect of SENSe therapy: We will evaluate the therapeutic gain in arm somatosensory function for stroke survivors (primary outcome) during the SENSe therapy phase compared to that of the usual care phase by estimating the mean within-person difference between the two trends and the associated 95% confidence intervals. The magnitude of change in arm somatosensory function under the two conditions will be calculated as a standardized effect size and compared to the benchmark effect size obtained in the original SENSe RCT (comparable cohort) [34]. Statistical estimates of change will be reported with 95% confidence intervals, and the extent of overlap across studies in these estimates of change will be described. Confidence intervals for the difference between mean change scores from the present and benchmarked study [34] will also be obtained. The analysis design will include the SENSe therapy center as a variable, to evaluate its potential systematic effect. Individual participant characteristics that may impact magnitude of therapeutic gain, such as age and time post-stroke, will be explored. Improvement in secondary outcomes, i.e., clinician-rated performance in valued activities, arm use, and quality of life, will also be evaluated pre–post therapy. Depending on verification of the normal distribution assumption, either a t-distribution or a bootstrapping method will be used to obtain the confidence interval. Maintenance of the intervention effect will be evaluated at the 12-week follow up (A4).

Treatment fidelity and behavior change: High fidelity delivery will be defined as a score of 80% or higher on the SENSe treatment fidelity checklists [43]. Audit data from treatment sessions will be independently summarized for each SENSe therapy treatment program delivered. The number of therapy deliveries achieving high treatment fidelity will be summarized. Pre- and post-implementation questionnaires of therapist knowledge, confidence, and ability to deliver SENSe therapy will be summarized and response tendencies will be examined using contingency tables, McNemar’s test, and graphical representation.

Therapist experience effect: The availability of 6 to 12 sequential cases treated with SENSe therapy by each of the 12 to 16 therapists will allow exploration of the hypothesis that a trend towards better outcomes arises with experience of therapy delivery. Individual therapeutic gain scores will be adjusted for initial sensory impairment, consistent with our prior analysis of which individual variables affect therapeutic gain [57]. Growth curve models will be explored for the sequence of adjusted therapeutic gains from each of the therapists (*n* = 12–16) to evaluate the autocorrelation structure of residuals and the viability of a common model. A pooled estimate of the effect of treatment experience will then be obtained via a meta-analysis, or hierarchical linear modelling if a common trajectory form is applicable.

Economic evaluation: We will report a cost description analysis for usual care and the SENSe therapy interventions and summarize these data as part of a cost consequence analysis [58] presenting the disaggregated costs and primary and secondary outcomes for stroke participants. The incremental cost-effectiveness of SENSe therapy compared to monitored wait list usual care will also be evaluated as the cost per achievement of improved arm somatosensory function (primary outcome for stroke survivor). We will also use simulation modelling to estimate the incremental cost per Quality Adjusted Life Year gained with SENSe therapy, drawing data from the study and the published RCT for SENSe [34]. One-way sensitivity and multivariable uncertainty analyses will be performed to assess the robustness of results. The findings from the economic evaluation will be used to inform business cases for future adoption of SENSe within the Australian healthcare context and may have relevance to other countries with similar funding models for healthcare. Results will be reported according to the Consolidated Health Economic Evaluation Reporting Standards (CHEERS) [59,60].

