#### 2.1.2. Specialist SENSe Therapy Centers and SENSe CONNECT Protocol

Four specialist SENSe therapy centers have been set up to deliver SENSe therapy to stroke survivors across three states in Australia. The new specialist therapy centers are linked with healthcare networks and universities or research institutes. The SENSe therapy centers will permit delivery of therapy to stroke survivors living in the community. Therapy may be delivered at the center or in the client’s home.

Occupational therapists and physiotherapists skilled and credentialled in SENSe therapy will deliver SENSe therapy to stroke survivors across the specialist therapy centers, using a pragmatic, within-subject wait list design [42]. The wait list design will evaluate change in outcomes over a 6-week period of usual care not associated with SENSe therapy, compared to a 6-week period of SENSe therapy delivered by credentialled therapists. During the wait list phase, participants will receive usual care, which will be monitored. Upper-limb therapy will not be restricted for participants during the control wait list phase; rather, participants will receive ‘usual care’ conditions [44]. Consistent with an independent review and analysis of ‘usual care’ usually received in health services in Australia (based on national audit and knowledge-translation study), this will usually not involve specific sensory rehabilitation, such as SENSe therapy [44]. Participants may continue to receive usual care during the SENSe therapy intervention period. Our prior controlled clinical trials provide evidence that exposure to sensory stimuli alone and/or current usual care is not usually sufficient to affect clinically significant improvement in somatosensory function [34,36,37]. All services and usual care received will be monitored.

Stroke survivors attending specialist SENSe therapy centers will be assessed on four occasions: baseline (i.e., Assessment 1, A1); after 6 weeks of usual care (i.e., A2); after 6 weeks of SENSe therapy (i.e., A3); and at follow up, 12 weeks post A3 (i.e., A4). All participants attending SENSe therapy centers will receive SENSe therapy (10 sessions) over a 6-week period. Assessors for health outcomes of stroke survivors will be blinded to study design and timing of therapy delivery. Researchers and statisticians involved in the data analysis will also be blinded to study design and timing of therapy delivery.

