SENSe therapists will not be blinded due to pragmatic reasons. It is planned that each therapist will deliver SENSe therapy to up to 12 stroke survivors. A secondary analysis will permit investigation of the association between stroke survivor outcomes achieved and the therapist’s amount of experience in delivering SENSe therapy. The study is approved by Austin Human Research Ethics Committee (HREC/18/Austin/153), and all experiments will be performed in accordance with the Declaration of Helsinki. Site-specific ethics approvals were also obtained. All participants will give voluntary informed consent.

Sample size: Stroke survivors—The SENSe CONNECT study design requires a within-subject, repeated measures analysis. The within-group analysis from the original SENSe randomized controlled trial (RCT) revealed a Cohen d of 0.366 for the somatosensory function outcome (repeated measures, small group *n* = 22/50; [34]). To achieve a within-group effect of d = 0.366 for a power of 0.8, a minimum sample of *n* = 61 is required. In the current study, the proposed sample size of *n* = 72 to 192 (i.e., 18 to 48 deliveries at each of the 4 centers) achieves this minimum and allows for dropout or poor recruitment. Assuming the variability in changes found in the SENSe RCT is replicated in the delivery of SENSe therapy, a maximum sample size of *n* = 192 will have a high degree of precision for estimating the effect size obtained within the SENSe therapy centers. The larger sample size will also facilitate generalizability of effect estimates to the broader target population of survivors of stroke living in the community. Therapists—At each specialist SENSe therapy center, it is planned that 3 or 4 therapists will each deliver SENSe therapy to 6 to 12 stroke survivors (i.e., 18 to 48 deliveries at each site; 72 to 192 across sites). A sample of 12 to 16 therapists was chosen to maximize replication across upskilled therapists while exploring the association between the amount of experience in delivery of SENSe therapy and therapy outcomes.

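### Computed as stated, the primary estimate leaves out every participant without A3; a repeated-measures likelihood model would estimate the same contrast from all observed visits

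*Protocol article*

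**What the plan says.** Section 2.8 (effect of SENSe therapy) defines the primary result for stroke survivors as "estimating the mean within-person difference between the two trends and the associated 95% confidence intervals". Later in the same paragraph, depending on a check of normality, "either a t-distribution or a bootstrapping method will be used to obtain the confidence interval". No other estimation method is named for this outcome. The section does name growth curve and hierarchical models, but for the therapist experience question.

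Section 2.1.2 and Table 1 set the visits: A1 at baseline, A2 after six weeks of usual care, A3 after six weeks of therapy, and A4 twelve weeks later.

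The sample size paragraph of section 2.1.2 reports that the earlier SENSe trial "revealed a Cohen d of 0.366 for the somatosensory function outcome" and concludes that "a minimum sample of *n* = 61 is required" for power 0.8. It adds that the planned 72 to 192 participants "achieves this minimum and allows for dropout or poor recruitment". No dropout rate is given. The limitations paragraph of the Discussion expects the pandemic to interrupt delivery of therapy.

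**The concern.** A mean of per-person differences between two trends exists only for people with all three visits. Everyone waits six weeks before therapy starts, so some loss after A2 is likely, and those people have already supplied A1 and A2.

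A2 enters the contrast with weight −2. If who leaves is related to the A2 score or to the change during usual care, those who remain have a selected A2, and the selection passes into the estimated benefit. There is no parallel control arm to absorb it. With higher scores meaning better function, loss of people who improved while waiting raises the estimate, and loss of people who worsened lowers it. The same estimate is then compared with the benchmark effect from the earlier trial and used in the cost-effectiveness analysis.

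**Working it through.** **1. The plan's own figure.** Inputs from section 2.1.2: d = 0.366, power 0.80. Alpha is not stated. Two-sided 0.05 is assumed, in line with the 95% intervals. A paired (one-sample) t-test with the noncentral t gives power 0.796 at n = 60 and 0.803 at n = 61, so 61 reproduces. The sample size therefore matches a t-test on one difference per person.

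**2. The estimator.** The article does not write out the weights. With equal phases, the difference between the two trends is (A3−A2)−(A2−A1) = A1−2·A2+A3. It cannot be computed without A3.

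**3. Assumptions for the size of the bias** (none is in the article): SD 1 at each visit, equal correlation ρ = 0.7, no change in usual care, true contrast 0.366 in single-visit SD units, 72 enrolled, higher score = better. The lowest planned total, 72, against the minimum of 61 leaves room for (72−61)/72 = 15.3% loss, so 15% is used, with 25% as a second case.
- SD of the contrast: √(6(1−ρ)) = √1.8 = 1.34.
- SE with 61 completers: 1.34/√61 = 0.172.
- On this scale 0.366 is 0.366/1.34 = 0.27 SD of the contrast. It is an illustration and not the protocol's d, which is standardized differently.

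**4. Bias of the completer mean.** With logistic dropout at rate p and log-odds b per SD of the driver, the completers' mean of the driver shifts by about b·p SD. At 15% this is 0.5 × 0.15 = 0.075 SD.
- *Driver = A1–A2 change.* Cov(contrast, A2−A1) = −3(1−ρ) and Var(A2−A1) = 2(1−ρ), so the slope is −1.5. Bias = 1.5 × 0.075 × √0.6 = 0.087, and 0.087/0.172 = 0.5 SE. For ρ = 0.6 and 0.8 the bias is 0.10 and 0.07. For simple A3−A2 the covariance is −(1−ρ), so its bias is one third as large.
- *Driver = A2 score.* Cov(contrast, A2) = −2(1−ρ) = −0.6. Bias = 0.6 × 0.075 = 0.045, twice that of simple A3−A2.
- *Driver = stable severity.* The weights 1, −2, 1 sum to zero, so the bias is about zero.

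**5. Simulation check** (n = 72, ρ = 0.7, log-odds 0.5 per SD; true value 0.366):

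| Who leaves | Loss | Completer mean | Likelihood estimate |
|---|---|---|---|
| Improvers on A1–A2 | 15% | 0.45–0.46 | 0.37 |
| Worseners on A1–A2 | 15% | 0.28 | 0.37 |
| Improvers on A1–A2 | 25% | 0.50–0.51 | 0.37 |
| Worseners on A1–A2 | 25% | 0.22–0.23 | 0.37 |
| Poor gain in therapy | 15% | 0.45 | 0.41 |
| Worse stable severity | 15% | 0.36 | 0.37 |
| Worse stable severity | 25% | 0.37 | 0.39 |

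**6. Precision under random loss.** The residual variance of A3 given A1 and A2 is 1 − 2ρ²/(1+ρ) = 1 − 0.98/1.7 = 0.424.
- 15% loss: the likelihood SE is about √[(1.8−0.424)/72 + 0.424/61] = 0.161, against 0.172 (6% smaller).
- 25% loss (54 completers): √[(1.8−0.424)/72 + 0.424/54] = 0.164, against 1.34/√54 = 0.183 (10% smaller).

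Simulation gives about 5–10%.

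**The case against.** The strongest reply is that this is a condensed article, that rules for missing data usually sit in the full protocol or SAP, and that section 2.8 states a quantity to be estimated and no complete-case rule. The sample size paragraph also calls for a repeated-measures analysis, and section 2.8 brings in center as a variable. Both are compatible with a mixed model. This stands in part: a missing imputation rule is no fault here, and the proposed model does not conflict with the article. But the article goes beyond silence. It names the estimator and the interval method, and the sample size matches a paired t-test. Followed as printed, that route cannot use a participant who has A1 and A2 only.

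A reader might infer three stronger things that the documents do not support.
- *That anyone who stops therapy is dropped.* A3 is scheduled by time, with no condition on sessions. The seven-session criterion governs the access outcome and therapist experience only. The point concerns missing A3, whatever the reason.
- *That the result is in general very sensitive to who leaves.* The bias is about zero when leaving follows stable severity, and about half a standard error in the 15% illustration.
- *That 15% is the protocol's dropout rate.* It is only the gap between 72 and 61, and the article lets that gap cover poor recruitment as well.

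It is also fair to say that the likelihood model's near-exact recovery in the first four table rows follows from dropout there depending only on A1 and A2, which is what that model assumes.

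**Conclusion.** The point holds as a weakness in the stated method with a nearly free remedy. Computed literally, the primary estimate discards A1 and A2 of everyone without A3. The consequence depends on the reason for leaving, which cannot be known in advance: about ±0.09 on a true 0.366 (single-visit SD units) at 15% loss driven by the A1–A2 change, about ±0.14 at 25%, roughly half that at 15% loss if driven by the A2 score, and none if driven by stable severity. A cost of about 5–10% in standard error remains even when loss is random. Correlation, loss rate and mechanism are all assumptions. The article neither shows that informative loss will occur nor rules it out.

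**What to change.** In section 2.8 (or the SAP), keep the contrast (A3−A2)−(A2−A1) and change how it is estimated: a likelihood-based repeated-measures model with visit as a factor, unstructured within-person covariance and center as already planned, fitted to all observed assessments. Report the contrast with its 95% interval. Keep the t/bootstrap analysis of participants with all three visits as a supporting analysis.

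The cost is wording only: no new data, visits or participants. The model assumes missing at random given the observed visits. If leaving depends on unobserved gain during therapy, it reduces the bias (from about 0.09 to 0.04 in the 15% illustration) but does not remove it. Where leaving follows stable severity it can be slightly off, by about 0.01–0.02 in simulation, while the completer mean is not. Reporting both analyses lets a reader see whether the choice matters.

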## 2. Materials and Methods

### 2.1. Study Design

The overall knowledge translation study involves a centralized hub, 4 specialist SENSe therapy centers, and 11 healthcare networks to deliver evidence-based upper-limb sensory rehabilitation for stroke survivors. The SENSe CONNECT arm detailed here is a prospective, pragmatic knowledge-translation study, involving four specialist SENSe therapy centers and stroke survivors in the community. Inclusion criteria are broad to test broader treatment effectiveness, and therapy will be delivered using a within-participant wait list control design [42].

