### 2.2. Participants

Participants for the SENSe CONNECT study include both therapists and stroke survivors.

Therapists: Inclusion criteria—Qualified occupational therapist or physiotherapist; current registration to practice; and willing to participate in the upskilling in SENSe therapy, undertake evaluation, and actively participate in mentoring and treatment fidelity activities to develop competency to deliver SENSe therapy. There are no additional exclusion criteria for the participants who are therapists. Replacement therapists will be recruited as needed. As a pragmatic implementation trial, restrictions will not be imposed on therapist participants’ experience or number of stroke survivors treated. However, demographic information for all therapist participants will be collected to ascertain relationships between stroke survivor outcomes and therapist characteristics.

Stroke survivors: People with stroke living in the community and presenting with new or chronic somatosensory impairment will be recruited. Stroke survivors may be referred via partner organizations, neurologists, rehabilitation physicians, general practitioners, other organizations, or self-referral. Inclusion criteria: A clinical diagnosis of stroke (including infarct or hemorrhage, people with a second stroke, no restriction on time since stroke); impaired touch sensation, limb position sense, and/or tactile object recognition of the upper limb, identified clinically and with screening tests; medically stable; able to give informed consent; able to comprehend simple instructions; willing to commit time to participate in the SENSe therapy program; and living in the community. Key exclusion criteria: Sensory impairment not due to stroke; severe unilateral spatial neglect (measured via line bisection and shape cancellation task); prior history of other central nervous system dysfunction with an unstable or progressive prognosis; severe to moderate cognitive impairment (i.e., not able to comprehend simple instructions or sustain attention needed to participate in treatment); not able to give informed consent; physical limitations that prevent participation in therapy tasks (e.g., contracture of the hand, or unhealed wounds); and unable to participate in a clinical appointment lasting 30 min. Thus, the design tests effectiveness with relatively unselected survivors of stroke in the community.

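### The supplementary benchmark against the original RCT has no case-mix adjustment and rests on an unsupported comparable-cohort label, so it cannot separate delivery from case mix

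*Protocol article*

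**What the plan says.** Section 2.8 (Effect of SENSe therapy) first defines the main estimate: the mean within-person difference between the SENSe phase and the usual-care phase. It then adds a comparison with an earlier trial. The standardized effect will be "compared to the benchmark effect size obtained in the original SENSe RCT (comparable cohort"), the overlap of the intervals across studies will be described, and "Confidence intervals for the difference between mean change scores from the present and benchmarked study [34] will also be obtained". In the same paragraph, participant characteristics such as age and time post-stroke are to be explored; initial impairment is not named.

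On who is enrolled, Section 2.1 says "Inclusion criteria are broad to test broader treatment effectiveness". Section 2.2 admits new or chronic impairment, any time since stroke, second strokes, and impairment in any one or more of touch, position sense and object recognition. It concludes: "Thus, the design tests effectiveness with relatively unselected survivors of stroke in the community".

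On what drives gain, Section 2.8 (Therapist experience effect) says: "Individual therapeutic gain scores will be adjusted for initial sensory impairment, consistent with our prior analysis of which individual variables affect therapeutic gain". The limitations in Section 3 say that survivor factors such as age, time since stroke and concomitant impairments are not controlled for, but are monitored and explored.

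The benchmark figure is in Section 2.1.2: the within-group analysis of the RCT "revealed a Cohen d of 0.366 for the somatosensory function outcome" ("repeated measures, small group *n* = 22/50").

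**The concern.** A comparison of outcomes between two separately recruited groups is informative about delivery only if the groups are alike in what determines gain, or if the comparison allows for the differences. The plan relies on the first condition and supports it only with a parenthetical label. The article gives no eligibility criteria, baseline severity or time since stroke for the RCT.

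The plan's own text gives reason to expect that case mix matters. It regards initial impairment as a determinant of gain and adjusts for it when comparing successive patients of one therapist. It attaches no such adjustment to the comparison between studies, where case mix has at least as much room to differ. The outcome index combines three tests (Section 2.4), while a person impaired in only one domain can enter (Section 2.2), so the starting level of the index may vary widely.

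The benchmark bears on whether newly upskilled therapists obtain an effect like that of the RCT. Unadjusted, a shortfall could be case mix taken for weaker delivery, and agreement could be weaker delivery offset by patients with more room to gain. Standardizing adds a second difficulty: d depends on the SD of the cohort as well as on the gain.

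**Working it through.** **1. The plan's own figure.** Section 2.1.2 states that, for d = 0.366, "for a power of 0.8, a minimum sample of *n* = 61 is required". Alpha is not stated; two-sided 0.05 is assumed. A paired t-test with the noncentral t distribution gives n = 61 (power 0.803), an exact match. The normal approximation gives 58.6, so 59. The sample size is therefore not at fault, and the match is consistent with d being mean change divided by the SD of change.

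**2. Effect of the SD alone.** With the same raw gain and an SD of change r times the RCT's, d = 0.366 / r. The values of r are assumptions; the documents give no SD.

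| r | d |
|---|---|
| 0.8 | 0.458 |
| 1.0 | 0.366 |
| 1.25 | 0.293 |
| 1.5 | 0.244 |

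The last two rows are apparent losses of 20% (1 − 1/1.25) and 33% (1 − 1/1.5) with no loss of effect. The first row shows that the movement can go the other way. A difference in raw mean change scores is not biased by this.

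**3. Effect of a shift in initial impairment.** If gain correlates ρ with initial impairment and the cohorts differ by s SDs in mean impairment, d moves by about ρ × s in either direction. Both inputs are assumed.

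- ρ = 0.2, s = 0.25: shift 0.05, d = 0.316 or 0.416
- ρ = 0.3, s = 0.5: shift 0.15, d = 0.216 or 0.516
- ρ = 0.5, s = 0.75: shift 0.375, d = −0.009 or 0.741

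This shift affects the raw mean change as well, so reporting mean change instead of d does not remove it.

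**4. Precision of the benchmark.** SE(d) = √(1/n + d²/(2n)), with the two studies independent. The article's notation leaves open whether the benchmark d rests on 22 or 50 patients, so both are shown.

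| RCT patients | 95% CI for 0.366 | Half-width of difference in d, CONNECT n = 72 | Same, n = 192 |
|---|---|---|---|
| 22 | −0.07 to 0.80 | 0.49 | 0.46 |
| 50 | 0.08 to 0.65 | 0.37 | 0.32 |

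A larger CONNECT sample helps little. With 22 RCT patients and n = 192 the variances are 0.0485 and 0.0056, so the RCT contributes 0.0485 / 0.0541, about 90%.

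**The case against.** The strongest reply has five parts.

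- **No contradiction is shown.** A reader might infer that broad entry criteria contradict the comparable-cohort label. They do not. Sections 2.1 and 2.2 describe CONNECT only, nothing in the article says the RCT was narrower, and the label might refer to a comparable subset of it. This stands: the label is unsupported, not shown to be false.
- **The benchmark is not the main test.** A reader might infer that the verdict on SENSe therapy hangs on the RCT. It does not. The main estimate uses each participant as their own control, and the benchmark has no margin or success rule. Delivery quality is also measured directly, by fidelity checklists and audits (Section 2.4). This stands and limits the weight of the point.
- **A raw-scale comparison is already planned.** This is true, and it answers the SD problem in step 2. It does not answer the shift in step 3.
- **The sizes are assumed and lie mostly within noise.** The changes in d from the larger SD ratios, 0.07 and 0.12, are well inside half-widths of 0.32 to 0.49. This stands as a caution about size. But bias from case mix does not shrink as CONNECT recruits more, and wide intervals make overlap with the RCT easy to obtain, so overlap alone says little.
- **Case mix is acknowledged, and covariates are analysis-plan detail.** Exploring age and time post-stroke within CONNECT does not adjust a contrast between studies. The choice of model can indeed be left to an analysis plan. The article, however, states the comparison, the ground for it, and an adjustment for initial impairment that it assigns to another analysis only.

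**Conclusion.** The point holds as a weakness of a supplementary comparison. As written, the benchmark contrasts CONNECT and the RCT without adjustment on a footing the article does not support, while the plan itself treats initial impairment as affecting gain. Neither agreement with the RCT nor a difference from it could be attributed to delivery.

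The size cannot be determined from the documents, which give no RCT baseline, SD of change or slope of gain on impairment. The figures in steps 2 and 3 are illustrations on assumed inputs. They show that a case-mix effect could range from negligible (0.05 in d) to about as large as the benchmark itself (0.375 against 0.366). It should not be inferred that the cohorts are in fact different, that d will fall, or that the within-person estimate of the SENSe effect is biased. None of these is shown.

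**What to change.** In Section 2.8:

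1. Delete the comparable-cohort label, or justify it with the RCT's eligibility criteria and baseline profile.
2. Tabulate initial impairment, age and time post-stroke for both studies side by side.
3. Make the already planned difference in mean change scores the main benchmark comparison. Adjust it for initial impairment, or standardize CONNECT to the RCT's distribution of initial impairment, and add age and time post-stroke where individual RCT data allow.
4. If a d is reported, divide by the same SD in both studies.
5. Label the unadjusted comparison descriptive. If individual RCT data cannot be obtained, label the whole comparison so.

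The cost is low on the CONNECT side. The three somatosensory tests are scheduled before therapy at A1 and A2 (Table 1), and age and time post-stroke are already named for analysis. The remedy depends on access to RCT baseline data, which the article does not promise, although Section 3 refers to a pooled analysis of individual differences covering age, severity and time post-stroke. The downside is modest extra analysis and a somewhat wider interval. Adjustment will not cure the imprecision in step 4, so the interval for the difference should be reported with that limit stated.
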